## Abstract

**Background:**

Adhesive small intestine occlusion [ASIO] is an important cause of hospital admission placing a substantial burden on healthcare systems worldwide. Often times, ASIO is associated with significant morbidity and mortality.

Icodextrin 4% solution [Adept, Shire Pharmaceuticals, UK] is a high-molecular-weight a-1,4 glucose polymer that is approved in Europe for use as an intra-operative lavage and a post-operative instillate to reduce the occurrence of post-surgery intra-abdominal adhesions.

There are no randomized trials on the use of this solution to prevent adhesions after ASIO operation in current medical literature.

The current clinical study evaluates the safety and effectiveness of Icodextrin 4% for decreasing the incidence, extent, and severity of adhesions in patients after abdominal surgery for ASIO.

**Design:**

The study project is a prospective, randomized controlled investigation performed in the Department of Transplant, General and Emergency Surgery of St. Orsola-Malpighi University Hospital [Bologna, Italy]. The study is designed and conducted in compliance with the principles of Good Clinical Practice regulations.

The study compares the results of Icodextrin 4% against a control group who does not receive anti-adhesion treatment. This randomized study uses a double-blind procedure to evaluate efficacy end points. In other words, designated third party individuals who are unaware of the treatment assigned to the patients to assess adhesion formation.

**Trial Registration Number:**

ISRCTN22061989

Prospective controlled randomized trial on Prevention of Postoperative Abdominal Adhesions by Icodextrin 4% solution after laparotomic operation for small bowel obstruction caused by adherences

[POPA study: Prevention of Postoperative Adhesions]

## Introduction

Adhesive small intestine occlusion [ASIO] is an important cause of hospital admission placing a substantial burden on healthcare systems worldwide. Often times, ASIO is associated with significant morbidity and mortality. Postoperative adhesions account for > 40 percent of all cases of intestinal obstruction, with 60 to 70 percent of those involving the small bowel [1]. Of patients who require multiple abdominal operation, 30 to 44 percent have adhesion-related intestinal obstruction [2]. For small-bowel obstruction, the incidence rises to 65 to 75 percent [3]. Mortality rates range from 3 percent for simple intestinal obstructions to 30 percent when the bowel becomes necrotic or perforated [3].

The overall recurrence rate for patients who underwent one operation for ASIO is 18% after 10 years and 29% at 30 years. For patients admitted several times for ASIO, the relative risk of recurring ASIO increased in relation to the number of prior ASIO episodes. The cumulative recurrence rate reached 81% for patients with 4 or more ASIO admissions [4]. In the US, adhesiolysis is responsible for > 300,000 hospitalizations annually, accounting for nearly 850,000 days of inpatient care and $1.3 billion in hospitalization and surgical expenditures [5].

An increasing number of adhesion-reduction agents, in the form of site-specific and broad-coverage barriers and solutions, are becoming available to surgical teams to complement optimal surgical techniques. Icodextrin 4% solution [Adept, Shire Pharmaceuticals, UK] is a high-molecular-weight a-1,4 glucose polymer that is approved in Europe for use as an intra-operative lavage and a post-operative instillate to reduce the occurrence of post-surgery intra-abdominal adhesions [6]. The icodextrin colloid is absorbed slowly, resulting in the retention of the fluid within the peritoneal cavity for more than 4 days. The solution reduces adhesions by a process of hydroflotation, keeping the peritoneal organs and tissues apart during the critical post-surgery period when the patient is at greatest risk of adhesion formation [7]. 1 Icodextrin has an extensive safety profile and has been used as a 7.5% solution in continuous ambulatory peritoneal dialysis [CAPD] for > 50,000 patient-years. In addition, preclinical and preliminary clinical studies have demonstrated the safety and efficacy of Icodextrin 4% solution in the reduction of adhesion formation following abdominopelvic surgery [8].

There are no randomized trials on the use of this solution to prevent adhesions after ASIO operation currently present in the medical literature.

The current clinical study evaluates the safety and effectiveness of Icodextrin 4% for decreasing the incidence, extent, and severity of adhesions in patients after abdominal surgery for ASIO.

## Methods

The project is a prospective, randomized controlled investigation performed in the Department of Transplant, General and Emergency Surgery of St. Orsola-Malpighi University Hospital [Bologna, Italy]. The study is designed and conducted in compliance with the principles of Good Clinical Practice regulations.

A computer-generated schedule creates the randomized assignments for the subject and control groups and the results are sealed in numbered envelopes. Participation in the study is requested after diagnosing small bowel obstruction caused by adhesions and determining if the patient fulfills the inclusion criteria [subjects who elect to undergo the surgical laparotomy]. Accordingly to the protocol, the patient signs a document indicating his or her consent and the responsible surgeon discloses the envelope.

If after opening the sealed envelope containing the assignments, the patient declines to enter the trial, the case is excluded from the study [all dropped-out patients are reported].

The responsible surgeon will record the patient's name [and number].

Each group has a sample size of 88 patients [176 patients for the whole study].

All randomized patients [Intention to Treat population] are included in the analysis.

Sample size has been calculated to reach a confidence level of 95% with a power of 80%.

A sample size of 88 patients each group [65 analyzable] is calculated supposing that the ASIO patients [first, second, third or fourth operation for ASIO] have a mean risk of 50% to develop a further episode of ASIO and this risk can be decreased by 25% [from 50% to 25%] with the use of Icodextrin 4%

Inclusion criteria are:

Adult patients [> 18 years]

Submitted to laparotomic surgical procedures for ASIO

Clinical and radiological evidence of adhesive small intestine obstruction

ASA I-III patients

Informed consent

Exclusion criteria

Intrabdominal cancer

Peritoneal contamination

IBD

Positive history of radiotherapy

Patients with an intra-operative findings of different pathology will be excluded from the study

Preoperative data include patient demographics, comorbid conditions [genitourinary, cardiac, pulmonary, gastrointestinal, renal, or rheumatologic] and a detailed history of previous occlusions and surgical procedures.

Decompression with a nasogastric tube is carried out in order to calculate the average nasogastric tube output of each patient [total amount of drainage/duration]. For patients administered Gastrografin before surgery, only the output before the procedure is considered. Intravenous fluid therapy is performed.

Plain abdomen X-rays are done and maximal small intestine diameter is calculated. Duration of symptoms before admission and number of previous operations are also evaluated.

Subjects with ASIO who elect to undergo the surgical laparotomy are enrolled in the study; written informed consent is obtained from each individual and then they are randomized into the study groups. Laparotomic surgical procedure is carried out and existing abdominal cavity adhesions are documented. Subjects are submitted to adhesiolysis with bowel resection if necessary with or without anastomosis. The first group receive traditional treatment [control group] whereas the second group is treated with Icodextrin 4% before abdomen closure. The use of irrigants during surgery is not allowed. Peritoneal contamination is evaluated with cultures.

Per protocol the abdominal fascia is closed with a running PDS suture and the skin is closed with sutures or skin staples.

Only one abdominal drainage in allowed in case of bowel resection and it has to be removed 7 days after the operation.

In case of bowel leakage, the patient will no longer be included in the study results.

For all patients, perioperative parameters are recorded, including blood loss, total length of the midline incision, method of anastomosis, method and timing of incision openings and closures, corticosteroid use. Operative wounds are classified as clean, clean contaminated, and contaminated as described by Schwartz [9].

Morbility, mortality and postoperative stay are registered. A flow chart showing the protocol is illustrated in figure 1.

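### The allocation envelope is opened before laparotomy although the arms differ only at closure, so adhesiolysis and intra-operative exclusions can be decided with the arm known

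*Protocol article*

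**What the plan says.** All places are in the protocol article, Methods, unless stated otherwise.

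- **Opening the envelope.** After the diagnosis and the check of inclusion criteria, "the patient signs a document indicating his or her consent and the responsible surgeon discloses the envelope". The description of patient flow gives the same order: "written informed consent is obtained from each individual and then they are randomized into the study groups".
- **Declining after opening.** "If after opening the sealed envelope containing the assignments, the patient declines to enter the trial, the case is excluded from the study". Such drop-outs are to be reported.
- **What follows.** "Laparotomic surgical procedure is carried out and existing abdominal cavity adhesions are documented". Then: "Subjects are submitted to adhesiolysis with bowel resection if necessary with or without anastomosis".
- **Where the arms part.** The control group has traditional treatment, whereas "the second group is treated with Icodextrin 4% before abdomen closure".
- **Exclusion at operation.** "Patients with an intra-operative findings of different pathology will be excluded from the study". Intra-abdominal cancer and peritoneal contamination are also exclusion criteria, and "Peritoneal contamination is evaluated with cultures".
- **Analysis population.** All randomised patients, named as the intention-to-treat population, are to be analysed.
- **Blinding.** The Abstract (Design) calls the procedure double-blind and explains this as assessment of adhesions by third parties unaware of treatment. Methods adds that a reoperation for obstruction is done by a surgeon blinded to the earlier anti-adhesion treatment. Neither statement concerns the index operation.

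**The concern.** The study treatment is a single act at the end of the operation, and no earlier step described needs knowledge of the arm. Yet the arm is disclosed before the first incision. Three kinds of decision then fall between disclosure and treatment:

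1. **How thoroughly adhesions are divided, and whether bowel is resected.** This can plausibly affect recurrent obstruction, a primary endpoint. If the surgery differs by arm, the comparison no longer isolates icodextrin.
2. **How existing adhesions are documented.** A baseline recorded with the arm known is a weaker basis for showing that the groups were alike.
3. **Who stays in the trial.** A different pathology found at operation leads to exclusion after randomisation, by someone who may know the arm. The same applies to cancer or contamination first seen then.

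Early opening also lets a patient leave after learning the allocation. In an open comparison, refusals of that kind need not be balanced between the arms.

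**Working it through.** **Step 1: order of events.** The main question is one of sequence.

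| Order | Event | Arm disclosed? |
|---|---|---|
| 1 | Consent | no |
| 2 | Responsible surgeon opens the envelope | yes |
| 3 | Patient may still decline | yes |
| 4 | Laparotomy, existing adhesions documented | yes |
| 5 | Adhesiolysis, resection if needed | yes |
| 6 | Exclusion for a different pathology found at operation | yes |
| 7 | Icodextrin or nothing, before closure | yes (first point at which it is needed) |
| 8 | Culture results, if they arrive later | yes |

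Row 3 settles the timing. A patient who can decline after the envelope is opened is awake, so the text cannot mean opening at closure.

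**Step 2: exclusions against the analysis population.** Rows 3, 6 and 8 can each remove a patient after randomisation. The same section says that all randomised patients are analysed. Both cannot hold for the same patient.

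**Step 3: does the sample size say how large the effect is?** First, the plan's own figure. Inputs: risks 50% and 25%, power 80%, and alpha 0.05, taken here as two-sided because the article does not say.

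- Uncorrected: n = [1.960 × √(2 × 0.375 × 0.625) + 0.842 × √(0.25 + 0.1875)]² / 0.25² = 57.7, so 58 per arm.
- With continuity correction: n = (57.7 / 4) × [1 + √(1 + 4 / (57.7 × 0.25))]² = 65.4, so 65 to 66 per arm. This matches the plan's 65 analysable.
- 66 / (1 − 0.25) = 88, the number randomised per arm. The 25% is inferred; the article states no loss rate.

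The allowance is 88 − 65 = 23 per arm (26.1%). The article does not say what these 23 are. Follow-up lasts 5 years, so loss to follow-up, death and withdrawal are obvious candidates, and removal for bowel leakage is another. The timing of the envelope changes none of them.

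**Step 4: an illustration of the mechanism, not an estimate.** Assumptions that are not in the document: no true effect, 50% risk in both arms, 88 randomised per arm, and a fraction x of extra exclusions in the icodextrin arm only, whose recurrence risk is r. The observed icodextrin risk is (0.50 − x·r) / (1 − x).

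| x | r | Observed risk | Chance of p < 0.05 |
|---|---|---|---|
| 0 | – | 50.0% | 5% |
| 10% | 70% | 0.43 / 0.90 = 47.8% | about 6% |
| 10% | 90% | 0.41 / 0.90 = 45.6% | about 9% |
| 15% | 70% | 0.395 / 0.85 = 46.5% | about 7% |
| 15% | 90% | 0.365 / 0.85 = 42.9% | about 15% |

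Under these assumptions the inflation is modest unless exclusion is both frequent and strongly selective. Exclusions of the opposite kind would hide a true benefit. Unequal adhesiolysis is not covered by this calculation, and the document gives nothing from which to size it.

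**The case against.** **The trial is described as double-blind.** That description is confined to third-party assessment and to the surgeon at a reoperation. Blinded assessment cannot undo unequal surgery or selective exclusion at the first operation. This objection does not stand.

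**The text says responsible surgeon, not operating surgeon.** This stands as a limit. That the two are the same person is the natural reading, but it is an inference. The point survives in a weaker form, because no passage separates the roles or conceals the allocation from the operator.

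**The intention-to-treat statement already prevents selective exclusion.** In part. If everyone randomised were analysed, selective exclusion would do no harm, so it would be wrong to say that analysis cannot deal with it. But the exclusion rules contradict that statement. Performance bias is different: intention-to-treat analysis does not touch it.

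**Not every exclusion is a surgeon's judgement made in theatre.** This stands. Only a different pathology is labelled intra-operative. Cancer may be known beforehand, and contamination is evaluated by laboratory culture. A reader might infer that several criteria can be judged only with the abdomen open; the text supports that for one, and allows that the other two may first appear then.

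**This is a condensed article, and its flow chart is not shown.** The point is not an omission. The article states the sequence twice, and a chart could not reverse it.

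**A tempting stronger reading is a gain in power.** Two-sided power at 50% versus 25% is 85.4% (Pearson) or 80.5% (continuity-corrected) with 65 per arm, and 93.7% or 91.5% with 88. A reader might infer that later opening would yield this gain with no extra enrolment. The document does not support that. The 23 losses per arm are not attributed to envelope timing, and patients with a different pathology never become analysable; their exclusion only moves to before randomisation.

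**Conclusion.** The point holds as a weakness of design. The allocation is disclosed before laparotomy, earlier than any described step requires, and the discretionary surgery and the exclusion for a different pathology follow with the arm open. This rests on the stated sequence and on one inference: that the operator is the surgeon who opens the envelope, or at least is not shielded from what it says.

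What follows is an opportunity for bias. A reader might go further and infer that bias occurred, or that it favours icodextrin; the document supports neither. Direction and size are unknown, and the figures in step 4 depend wholly on assumed inputs. The required sample size does not change. Because the remedy is simple and removes the opportunity before treatment is given, this is best classed as a cheap improvement.

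**What to change.** - Take consent before surgery, as now.
- Keep the numbered envelope sealed until adhesiolysis and any resection are complete, existing adhesions are documented, and the surgeon has recorded that the intra-operative eligibility criteria are met.
- Open it immediately before closure, for example by a circulating nurse, and define that moment as randomisation.
- Analyse everyone randomised, including patients whose culture results arrive later.
- Delete the provision for excluding patients who decline after the envelope is opened before surgery; with late opening that situation no longer arises.

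Removal from the results for bowel leakage is not affected by envelope timing. It also conflicts with the intention-to-treat statement and has to be reconciled separately.

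**Cost.** A change of protocol wording and a small theatre routine. Some consented patients will be found ineligible at operation and never randomised, so slightly more than 176 must be consented to randomise 176. The document gives no rate from which to say how many. Treatment in either arm is unchanged.

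### Trial entry stays open after the allocation is seen: the responsible surgeon opens the envelope, and no described step ties the patient to it beforehand

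*Protocol article*

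**What the plan says.** The protocol article's Methods section sets out the allocation procedure in this order.

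- Preparation: "A computer-generated schedule creates the randomized assignments for the subject and control groups and the results are sealed in numbered envelopes".
- Consent and opening: "the patient signs a document indicating his or her consent and the responsible surgeon discloses the envelope".
- Exit after opening: "If after opening the sealed envelope containing the assignments, the patient declines to enter the trial, the case is excluded from the study". A bracketed remark adds that drop-outs are all reported.
- Recording, in a separate one-line paragraph: "The responsible surgeon will record the patient's name [and number". No time relative to the opening is given, and no place of recording.

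Further on, Methods repeats the order of consent and allocation: "written informed consent is obtained from each individual and then they are randomized into the study groups". The analysis set is stated as: "All randomized patients [Intention to Treat population] are included in the analysis".

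Opening and recording are both given to the responsible surgeon. The requests for participation and for consent are written in the passive, with no actor named.

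**The concern.** Allocation concealment requires that a patient be irrevocably in the trial, at a known place in the sequence, before anyone involved learns the arm. The described procedure does not secure this. A treating clinician breaks the seal. The decline sentence treats a patient whose envelope is already open as someone who has not yet entered. The only recording step mentioned comes after both in the text. An opened envelope could therefore go unused or be given to another patient, and nothing described would prevent it.

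This differs from how known drop-outs are analysed. An intention-to-treat rule can keep a patient whose allocation was logged. It cannot recover one who was never linked to an envelope.

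The risk is not abstract in this trial. The Introduction says recurrence risk increases with the number of prior episodes, and Methods collects a detailed history of previous occlusions before surgery. A strong prognostic factor is thus visible to the person who opens the envelope. The blinded third-party surgeon assesses adhesions at reoperation and cannot undo selection at entry.

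**Working it through.** **The plan's own figure.** Inputs from Methods: risks of 50% and 25%, 95% confidence (taken as two-sided 5%), 80% power.

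- Pooled formula: n = [1.960·√(2·0.375·0.625) + 0.842·√(0.25 + 0.1875)]² / 0.25² = (1.342 + 0.557)² / 0.0625 ≈ 57.7, so 58 per group.
- With continuity correction: n′ = (57.7/4)·[1 + √(1 + 4/(57.7·0.25))]² ≈ 65.4, so 66 when rounded up. The plan states 65 analysable.
- Implied loss: 1 − 65/88 = 26.1%.

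The sample size reproduces to within one patient. The concern is procedural and changes none of these figures.

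**The procedure, step by step.**

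| Step | What Methods states | Does it bind the patient to an envelope before opening? |
|---|---|---|
| Envelopes | Sealed and numbered | Only if used in order and reconciled; neither is stated |
| Consent | Signed before opening | No; it shows willingness but gives no envelope number |
| Opening | By the responsible surgeon | No |
| Decline | Possible after opening; case excluded | No; it keeps entry open |
| Recording | By the responsible surgeon, time not given | Not as written |

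**Illustration of size.** Inputs:

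- Mean risk of 50% in both arms: the plan's control risk, with no treatment effect.
- Extremes of 18% and 81%, from the Introduction.
- Share f of places in each arm affected: an assumption, as the document gives no figure.
- Test: two-sided 5% chi-squared without continuity correction. Rejection probabilities are exact, summed over both binomial distributions.

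*Selected patients replace average ones.* Risk in one arm = (1 − f)·50% + f·81%; in the other = (1 − f)·50% + f·18%.

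- f = 10%: 45% + 8.1% = 53.1% versus 45% + 1.8% = 46.8%. The difference is 6.3 points.
- f = 5%: 47.5% + 4.05% = 51.55% versus 47.5% + 0.9% = 48.4%. The difference is 3.15 points.

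*Upper bound: full swap, where each displaced patient is the opposite extreme.* Shift per arm = f·(81% − 18%).

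- f = 10%: 50% ± 6.3%, that is 56.3% versus 43.7%. The difference is 12.6 points.
- f = 5%: 50% ± 3.15%, that is 53.15% versus 46.85%. The difference is 6.3 points.

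| Scenario | False difference | False-positive rate, 88 per arm | 65 per arm |
|---|---|---|---|
| No selection | 0 | 5.5% | 4.4% |
| Replacement, f = 5% | 3.15 points | 7.6% | 5.8% |
| Replacement, f = 10% | 6.3 points | 14% | 10% |
| Full swap, f = 5% | 6.3 points | 14% | 10% |
| Full swap, f = 10% | 12.6 points | 40% | 28% |

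At 88 per arm, f = 10% is about 9 patients in each arm (8.8).

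**The case against.** The strongest reply is that this is operational detail which a condensed article may leave to the full protocol. Strict sequential use, a custodian, a central log and final reconciliation are such details, and their absence alone would be no finding. This part of the objection stands. The point survives because the article does more than stay silent: it states who opens, who records, and that entry may be declined after disclosure. Its weakness lies in that stated procedure.

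A reader might also infer four stronger things that the text does not support.

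- **That identity is recorded only after opening.** The recording sentence gives no time. The order is inferred from where the sentence stands, and recording at or before opening is compatible with it.
- **That one surgeon recruits, opens and records.** Only opening and recording are assigned to the responsible surgeon. Who recruits or takes consent is not stated.
- **That misuse would leave no trace.** Numbered envelopes, consent signed before opening and reported drop-outs are all traces. A gap in the numbers, or a consent form with no matching entry, could show. These limit free matching but do not prevent it.
- **That the false-positive rate would be 40%.** This requires a full swap of opposite extremes in 10% of places. If selected patients replace average ones, the rate is 14%.

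The two extremes also rest on different bases. The 18% is a 10-year figure after one operation. The 81% is a cumulative rate for patients with four or more admissions, with no time stated. Follow-up here is 5 years. The figures therefore show scale and are not estimates.

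**Conclusion.** The concern holds in limited form. As described, the responsible surgeon opens the envelope and records identity, a patient may decline after the arm is known and is then excluded, and no step fixes patient to envelope beforehand. Trial entry thus stays open after disclosure, which weakens concealment.

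The size cannot be known from the document. Under the assumed 10% share, the replacement scenario is the one to cite, with the full swap only as an upper bound; at a 5% share the replacement effect is small. All of these figures assume selection in opposite directions in the two arms. Nothing in the document suggests that selection is intended or has happened. The conclusion rests on the stated procedure and not on the illustration.

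**What to change.** Replace the recording sentence with a timed rule. After consent, the patient's name, study number, date and time are entered against the next unopened envelope in sequence, and only then is it opened. The patient counts as randomised from that entry, whatever happens next. At the end, all 176 envelope numbers are reconciled against the log.

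This also gives the intention-to-treat sentence a clear starting point: a patient who declines after opening is a randomised patient who withdrew, and not a case that never entered. The exclusion sentence should be reworded to match.

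The cost is one reworded passage, a log sheet and about a minute per patient. Sample size and clinical care are unaffected. Having someone who is not treating the patient hold the envelopes would add protection but is optional.

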**Figure 1 F1:**
[figure not shown]

The patients are followed-up for 5 years.

In case of reoperation for ASIO the procedure is carried out by a third party blinded to the patient's previous antiadhesive treatment: this surgeon evaluates incidence, location, severity, and extent of adhesions. The incidence of adhesions is assigned a severity score of 0 [no adhesions], 1 [filmy thickness, avascular], 2 [moderate thickness, limited vascularity], or 3 [dense thickness, vascularized].

Adverse events [AEs] are collected for the duration of the study, beginning at the time of randomization.

AEs are identified and described by the primary investigators.

In the control group, patients will be treated as in our daily surgical practice.

In the informed consent form, patients receive all the information about the study protocol, confidential data management and they fill up a questionnaire before signing or refuse.

There are not inconveniences caused to the patients. No incentives are planned for the patients regarding the operation or the follow-up.

There are not any additional risks for the treatment and control group: both groups have the standard surgical treatment and follow-up: icodextrin group is an antiadherences fluid with no adverse effects.

All the medical information obtained from the patients are kept confidential among the research scientists conducting the study.

The patients are free to withdraw from the study, whenever they want and without any obligation.

The study is approved by the ethical Committee of the S'Orsola-Malpighi Hospital, Bologna, Italy

The primary endpoints of our study are:

To evaluate the therapeutic role of Icodextrin 4% to reduce ASIO incidence

To reduce adherences rate [in case of reoperation for ASIO]

The onset of any other complications are recorded intraoperatively, postoperatively, at discharge, at 7-days, 1-month, 6-months, every year up to 5 years follow-up.

The primary outcomes are assessed every year [interim analysis] up to 5 years after the last enrolled patient.

The data generated by this study are analysed in two ways. The continuous numerical data are subjected to analysis of variance [ANOVA], this method being applicable to the discrimination of two continuous populations. Discrete data are analysed by the chi-squared test or Fisher exact test, as appropriate. Statistically significant differences between study treatments are based on p < 0.05.

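### Number of prior ASIO episodes is reported as prognostic and is recorded, but the named test leaves it out; stratifying would gain some power at almost no cost

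*Protocol article*

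**What the plan says.** Four statements in the protocol article bear on this point.

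- **Introduction.** Recurrence after one operation is 18% at 10 years and 29% at 30 years. For patients admitted repeatedly, "the relative risk of recurring ASIO increased in relation to the number of prior ASIO episodes", and the cumulative figure is 81% with four or more admissions.
- **Methods, sample size.** The calculation is made "supposing that the ASIO patients [first, second, third or fourth operation for ASIO] have a mean risk of 50" per cent. The treatment effect is that "this risk can be decreased by 25% [from 50% to 25%] with the use of Icodextrin 4" per cent solution.
- **Methods, preoperative data.** The data collected include "a detailed history of previous occlusions and surgical procedures". The number of earlier operations is also evaluated.
- **Methods, statistical paragraph after Figure 1.** "Discrete data are analysed by the chi-squared test or Fisher exact test, as appropriate", and "Statistically significant differences between study treatments are based on p < 0.05".

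Allocation is by a computer-generated schedule in sealed, numbered envelopes. The text does not say whether the schedule is stratified. No stratified or covariate-adjusted analysis is named.

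**The concern.** The protocol identifies a baseline factor that predicts the primary outcome and collects it on every patient, but names a test that does not use it. Two things follow when a prognostic factor is left out of a binary comparison.

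- Outcome variation that the factor could explain stays in the error term, so power is lower than it could be with the same patients.
- If one arm happens to receive more patients with many earlier episodes, the observed difference in recurrence moves with it, and the estimate is not corrected.

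The stake is the precision and credibility of a single trial with 88 randomised and 65 analysable patients per arm. Because the test is named in the protocol, a switch to an adjusted analysis after the data are seen would be open to question. The time to decide is beforehand.

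**Working it through.** **Inputs from the protocol article**
- Methods: "Sample size has been calculated to reach a confidence level of 95% with a power of 80" per cent; control risk 50%, treated risk 25%; "A sample size of 88 patients each group [65 analyzable"], 1:1.
- Introduction: 18% and 81% as the ends of the risk gradient.

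**Assumed, not in the documents**
- The share of patients in each prior-episode group, the middle risks, and that the Introduction's figures carry over to the trial's 5-year follow-up.
- A two-sided 5% level and a common odds ratio across groups.

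**Step 1: reproduce the stated size.** For two proportions with pooled variance under the null:

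n = [1.96·√(2·0.375·0.625) + 0.8416·√(0.25 + 0.1875)]² / 0.25² = (1.342 + 0.557)² / 0.0625 ≈ 57.7

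With continuity correction: n′ = (57.7/4)·[1 + √(1 + 4/(57.7·0.25))]² ≈ 65.4, so 66 against the stated 65. A loss of 26% takes 65 to 88. Exact power at 65 per arm is 80.9% (Fisher), 80.5% (continuity-corrected chi-squared) and 85.4% (uncorrected chi-squared). The stated size is therefore that of an unadjusted two-proportion test, and it delivers the stated 80%.

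**Step 2: how much the factor explains.**
- Steep gradient, four equal groups at 18, 40, 60, 81%: mean 49.75%; variance of the group risks (31.75² + 9.75² + 10.25² + 31.25²)/4 = 546 points². Share of outcome variance: 546/(49.75·50.25) = 22%.
- Flat gradient, four equal groups at 35, 45, 55, 65%: variance 125 points²; share 125/(50·50) = 5%.

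**Step 3: chance imbalance.** Under simple randomisation, the difference between arms in expected control risk has SD = √(2·variance/n).
- Steep: √(2·546/65) = 4.1 points at 65 per arm; √(2·546/88) = 3.5 at 88.
- Flat: √(2·125/65) = 2.0 points at 65 per arm.

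With a near-identical steep gradient (18, 39, 60, 81%), simulated imbalance at 65 per arm exceeds 5 points in 22% of trials and 10 points in 1.7%.

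**Step 4: power at the planned effect.** Simulation, with the common odds ratio chosen so that the overall treated risk is 25% (about 0.257 for the steep gradient). The stratified statistic is

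z = Σ(xₖ − n_ck·Mₖ/Nₖ) / √Σ[n_ck·n_tk·Mₖ(Nₖ − Mₖ)/(Nₖ²(Nₖ − 1))]

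Here, in group k, xₖ is control recurrences, n_ck and n_tk are the arm sizes, Mₖ is all recurrences and Nₖ is all patients. Neither test is continuity-corrected.

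| Control risks (mix) | 65 per arm: chi-squared / stratified | 88 per arm: chi-squared / stratified |
|---|---|---|
| 18, 40, 60, 81% (equal) | 84.8 / 90.2% | 93.5 / 96.7% |
| 18, 81% (49:51), the extreme case | 85.8 / 95.2% | 93.9 / 98.8% |
| 35, 45, 55, 65% (equal) | 85.4 / 85.4% | 93.7 / 94.0% |
| 40, 60% (equal) | 85.4 / 85.7% | 93.8 / 94.3% |
| 18, 39, 60, 81% (50:25:15:10) | 65.1 / 72.0% | 78.0 / 84.4% |

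The last row departs from the plan. Its control mean is 0.50·18 + 0.25·39 + 0.15·60 + 0.10·81 = 35.9%, and the treated risk is half of that.

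**Step 5: type I error.** With no treatment effect, the unadjusted test rejects in 4.4 to 5.6% of trials and the stratified test in about 5%.

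**The case against.** The strongest reply is that nothing here is an error. The 50% is openly a mean over operation histories, so the mixture was averaged over and not overlooked. The chi-squared test matches the basis of the sample size, and randomisation keeps it valid, because chance imbalance is already allowed for in its error rate. All of this stands.

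Three further points stand in part.

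- **The gradient is uncertain.** The 18% is a 10-year figure, the 81% has no stated horizon, and follow-up is 5 years. The Introduction counts admissions and episodes, while the sample-size passage counts operations. The documents also do not rank this factor against others. The gain must therefore be shown as a range that includes nil.
- **Adjustment is often left to the analysis plan.** That is true, and the sentence on discrete data is general. But it does name the tests, and this endpoint falls under it. The point concerns a choice that was made, not a missing detail.
- **The trial might look underpowered.** A reader might infer this because, with the steep gradient and 88 per arm, a common odds ratio of 0.40 gives only 65.5% unadjusted and 72.8% stratified. That odds ratio implies a treated risk of 32.4%, and an odds ratio of 0.33 implies 29.1%. Neither is the planned 25%, so these figures do not show a shortfall against the plan.

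**Conclusion.** The point holds as one of efficiency. The protocol reports a prognostic gradient, records the factor and names a test that does not use it. At the planned 50% versus 25%, stratifying is worth about 5 points of power at 65 per arm and 3 to 4 at 88 under the assumed four-group steep gradient. It is worth about 7 points (6 to 7) if most patients are at a first operation and risk is halved, and 0 to 0.5 points under a flat gradient. The SD of chance imbalance at 65 per arm is about 4 points with the steep gradient and 2 with the flat one.

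Two stronger readings are not supported. The unadjusted test is not invalid or biased, since its error rate stays near 5%. The sample size is not wrong, since it reproduces and gives the stated 80%.

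Confidence is moderate, because the group mix, the middle risks and the 5-year gradient are assumptions.

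**What to change.** State in the analysis section that the primary comparison of ASIO recurrence is a Mantel-Haenszel test stratified by the number of previous ASIO episodes, with the unadjusted chi-squared or Fisher test as a sensitivity analysis. Fix the categories in advance, for example none, 1, 2, and 3 or more. Say whether episodes, admissions or operations are counted, since the article uses all three.

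The cost is a sentence or two. The history is already collected, and no patients or visits are added. If the gradient proves flat, the simulations show no loss of power. Stratified envelopes (first versus repeat operation) are optional. No change to a time-to-event analysis is required for this point.
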